#### Interventions

The *Healthy Divas* intervention was developed to address the unique HIV care needs of TWH by providing relevant information, support, and skills building for the identification and accomplishment of individualized healthcare goals related to both gender transition and HIV care and treatment. *Healthy Divas* consists of 6 peer-led individual sessions and one peer-led group workshop of 3–7 participants attended by a healthcare provider with expertise in HIV care and transgender health. As a group, participants have the opportunity to ask questions and receive accurate information and guidance to address barriers to engagement in healthcare. The intervention supports TWH in optimizing their health outcomes by increasing healthcare empowerment with a gender-specific and affirming approach. For example, in *Healthy Divas*, TWH build skills to cope with transphobia and HIV stigma, become active and collaborative in their treatment planning, and proactively address challenges to adherence and in their relationships with providers. *Healthy Divas* also incorporates transgender-specific concerns about substance use, provides opportunities for a participant to consider how substance use might be affecting her ability to reach her personal health goals, and supports her ability to access culturally competent treatment if she identifies this as a need.

The combination of individual sessions and a single group workshop permitted tailoring and flexibility to address the specific concerns of each participant while also capitalizing on a supportive group process with the presence and contribution of knowledgeable providers. Each intervention session was standardized through the use of a detailed facilitator manual specifying session content, procedures, exercises, and activities (see Table 1 for *Healthy Divas* intervention activities outline).

**Table 1 T1:** *Healthy Divas* intervention activities outline.

**Topics**	**Participant activities**

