#### Choice of Comparators

For our control condition, we considered several alternatives and weighed several issues, including Safer and Hugo's guidance for identifying active intervention elements while controlling for potential confounding effects (45). When considering a time and attention matched control condition, we found that identifying an inert intervention that would not directly or indirectly tap into the constructs of gender affirmation and healthcare empowerment through discussions of topics of interest was a challenge. Such a control intervention may have had non-specific effects that threatened our power to detect effects of the *Healthy Divas* intervention. Therefore, we decided on a treatment as usual (TAU) control condition in which participants randomized to the control condition were offered the intervention content after their final assessment point. As part of this design, we used measures to assess and control for exposure to adherence counselling and support outside of the trial for TWH in both conditions (46). We also accounted for variability in the treatment as usual control condition by assessing standard care quality (SCQ), as described by de Bruin et al., and used the SCQ measure as a covariate in our analyses of intervention effects. (46, 47) Recognizing that an effect on outcomes using this design will provide useful but incomplete evidence for this intervention, we identified potential future steps to evaluate the effectiveness of this intervention in comparison to other approaches. Given the relative strengths and weaknesses of any choice of control condition, our design represents a critical next step in the development of the evidence base for a high-risk population with disparately poor HIV outcomes.

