### Trial Design

This study was designed as an interventional 2-arm randomized controlled superiority clinical trial with two parallel groups and a 1:1 allocation to compare *Healthy Divas* to a TAU control condition. The *Healthy Divas* intervention is a combination of six individual sessions with a peer counsellor and a peer-led small group workshop with other TWH, and a provider with expertise in HIV primary care and transgender healthcare, all completed within 3 months. TWH (*N* = 278) were enrolled at two sites (117 in San Francisco; 161 in Los Angeles) who were confirmed to be living with HIV and showed evidence of suboptimal engagement in care, defined as meeting one or more of the following three indicators: (a) not on ART, (b) on ART but reporting non-adherence, (c) reporting no HIV care appointments in the prior 6 months. The primary outcome was virologic control, defined as undetectable viral load. Secondary exploratory outcomes were (a) within-subject improvement in scores on our engagement in HIV clinical care composite index, which includes ART uptake, ART adherence, and self-reported attendance at HIV primary care appointments; and (b) change in hypothesized mechanisms of action (e.g., healthcare empowerment, gender affirmation). The intervention began immediately following randomization and was completed prior to the 3-month follow-up assessment. Follow-up assessments, including viral load assays and surveys, occurred for 12 months post-randomization at 3-month intervals (see Figure 1 for the Schedule of enrolment, intervention, and assessments). Monthly check-in visits promoted contact between visits and allowed regular monitoring of HIV medical care.

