Therefore, we hypothesized that, following the intervention, the odds of undetectable viral load will be higher for intervention participants than for control participants (Hypothesis 1). Our primary interest was to estimate the marginal or population-average effect of intervention participation on each outcome rather than the effect for a hypothetical average subject. (93) Moreover, within-subject correlations among outcomes are considered nuisance parameters rather than quantities of interest to be modeled explicitly. Accordingly, generalized estimating equations (GEE) will be used to perform the proposed primary analysis, which is a planned time-averaged comparison of post-baseline measurements across the intervention and control groups to test primary Hypothesis 1. Alpha will be set at 0.05 for this planned comparison. Any additional *post-hoc* comparisons (e.g., paired comparisons of the control and intervention groups at each time point) will maintain a nominal alpha level of 0.05 through the use of simulation-based stepdown multiple comparison methods (94). Reflecting the binary nature of the virologic control outcome, a binomial distribution and logit link will be used for this analysis. Though GEE estimates are consistent even if the correlation structure is misspecified, GEE's statistical efficiency improves as the working correlation structure more closely approximates the actual correlation structure (95). Thus, working correlation structures suitable for the study's design will be considered (e.g., unstructured, AR (1), exchangeable, *M*-dependent) (96). The QIC statistic will be used to select the final working correlation structure (97). Robust Huber-White “sandwich” standard errors will be used to obtain correct inferences even if the chosen correlation structure remains slightly misspecified. GEE case deletion diagnostics (e.g., DFBetas, Cook's *D*) will be used to investigate whether influential cases are present; if such cases are found, results will be reported with and without influential cases included (98). As noted above, standard care quality (SCQ) will be included as a covariate in this analysis. In addition, randomization strata indicators will be included as covariates to obtain unbiased results (99). Additional covariates may be included if they improve QIC.

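### The intervention is delivered in shared workshops and by shared counsellors in one arm only, but the primary GEE and the power table allow only for within-subject correlation, so the standard error is too small if outcomes differ between delivery groups

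*Protocol article*

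**What the plan says.** **Delivery.** The Trial Design section describes "six individual sessions with a peer counsellor and a peer-led small group workshop with other TWH". The Interventions section gives the workshop size: "6 peer-led individual sessions and one peer-led group workshop of 3–7 participants". It presents the group as part of how the intervention works, "capitalizing on a supportive group process with the presence and contribution of knowledgeable providers". Under Choice of Comparators, the control arm is treatment as usual, and "participants randomized to the control condition were offered the intervention content after their final assessment point", so controls have no delivery groups during follow-up. Allocation is by individual, with "two parallel groups and a 1:1 allocation".

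**Analysis.** Statistical Methods, Outcomes, sets the primary test as a "planned time-averaged comparison of post-baseline measurements across the intervention and control groups to test primary Hypothesis 1", using a logistic GEE. The only dependence it names is within the participant: "within-subject correlations among outcomes are considered nuisance parameters rather than quantities of interest to be modeled explicitly". The working structures listed as examples (unstructured, AR(1), exchangeable, M-dependent) are the usual ones for repeated measures. Robust "sandwich” standard errors will be used to obtain correct inferences even if the chosen correlation structure remains slightly misspecified". The named covariates are standard care quality and the randomisation strata. Workshop and counsellor do not appear.

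**Power.** The Sample Size section uses 114 analysed participants per group, four post-baseline measurements and a within-subject correlation of 0.20 to 0.80. It has no term for correlation between participants.

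**The concern.** This is a partially nested design: one arm is grouped by delivery and the other is not. Workshop topics came from the participants in each group, and counsellors were trained to be flexible within the manual. Both give a route by which outcomes could differ from one delivery group to another.

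A sandwich variance protects against a wrong working correlation inside the chosen cluster. If the cluster is the participant, which is the natural reading of the text, the covariance between two participants in the same workshop or with the same counsellor is set to zero, whichever working structure QIC selects. Site, age and race strata as main effects do not remove it, because it arises within strata and in one arm only.

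At stake is the standard error of the single primary test at alpha 0.05. The point estimate is not biased by this. The confidence interval could be too narrow, and a borderline result could turn on it.

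**Working it through.** **1. Reproduce the plan's own figure.** Inputs from Sample Size: n = 114 per arm, 4 measures, alpha 0.05 (two-sided reproduces the table), power 0.80. The variance factor for the mean of four exchangeable measures is D = (1 + 3ρ)/4; at ρ = 0.50, D = 0.625. Power comes from the pooled two-proportion formula with 114/D per arm.

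- P0 = 0.30, difference 14.1%: power 0.799, OR 1.84, h 0.293. Table 5 gives 1.84 and 0.293.
- P0 = 0.80, difference 10.4%: power 0.801, OR 2.35, h 0.297. Table 5 gives 2.35 and 0.297.

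Over all rows of these two columns, the recomputed difference is within 0.05 percentage points of the table. The middle column, headed 0.55, reproduces at P0 = 0.50; that is a separate matter, but it is why 0.50 is used in step 5. Table 5 is therefore fully explained by within-subject correlation, with no allowance for delivery groups.

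**2. Add clustering in the intervention arm only.** Let k be the delivery-group size and ICC the between-participant correlation of the time-averaged outcome within a group. **The ICC is an assumption throughout.**

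- DEFF = 1 + (k − 1) × ICC, applied to the intervention arm.
- With equal arms and a zero average effect, true SE / participant-level SE = √((1 + DEFF)/2).
- Actual two-sided type I error = 2 × (1 − Φ(1.96 / ratio)).

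**3. Workshops** (the document gives k = 3 to 7; k = 5 is the midpoint):

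| k | ICC | DEFF | SE ratio | Type I error |
|---|---|---|---|---|
| 5 | 0.01 | 1.04 | 1.010 | 5.2% |
| 5 | 0.05 | 1.20 | 1.049 | 6.2% |
| 5 | 0.10 | 1.40 | 1.095 | 7.4% |
| 3 | 0.01 | 1.02 | 1.005 | 5.1% |
| 7 | 0.10 | 1.60 | 1.140 | 8.6% |

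**4. Counsellors** (number not given; 4 assumed, so 114/4 = 28.5, taken as k = 28):

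| ICC | DEFF | SE ratio | Type I error |
|---|---|---|---|
| 0.01 | 1.27 | 1.07 | 6.6% |
| 0.02 | 1.54 | 1.13 | 8.2% |
| 0.05 | 2.35 | 1.29 | 13.0% |

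With 8 counsellors (114/8 ≈ 14 each) the range for ICC 0.01 to 0.05 is 5.8% to 8.9%.

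A simulation of 20,000 trials per setting, with normally distributed participant means, agrees. For k = 5 it gives 5.5%, 6.3% and 7.7% at ICC 0.01, 0.05 and 0.10, against 5.2% with no clustering. For k = 28 it gives 6.7%, 8.2% and 13.0% at ICC 0.01, 0.02 and 0.05, against 5.1%.

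**5. Power once clustering is accounted for** (P0 = 0.50, ρ = 0.50, at the effect planned for 80%, a difference of about 14.5%):

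- workshops of 5, ICC 0.05: power 0.76, minimum detectable difference 15.1%;
- workshops of 7, ICC 0.10: power 0.69, minimum detectable difference 16.4%;
- 28 per counsellor, ICC 0.02: power 0.70, minimum detectable difference 16.2%.

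**The case against.** **The article condenses a fuller plan.** It never says in words that participants are independent, its list of working structures is introduced as examples, and facilitator clustering is often left to the analysis plan. This has some force. But the primary GEE is set out closely (link, working correlations, QIC, sandwich errors, deletion diagnostics, covariates) with one source of dependence named, and the power table reproduces with no clustering. That is a stated analysis, not only a missing detail.

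**The null matters.** Participants were individually randomised. If the intervention changes nobody's outcome, workshops and counsellors cannot create differences, and the participant-level comparison is valid. Inflation needs an average effect of zero with some delivery groups doing better and others worse. This stands in full.

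**Features that limit clustering.** There is one workshop against six individual sessions, a detailed facilitator manual, weekly group supervision and a laboratory outcome. This also stands, and it makes a small workshop effect likely.

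**Stronger readings that the document does not support.**

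- A reader might infer that the primary test's type I error definitely exceeds 5%. No ICC is given, so this is conditional.
- A reader might infer that the error favours the intervention. A standard error that is too small leaves the estimate unbiased and raises false rejections in both directions.
- A reader might take the highest rates as the expected size. They come from counsellor clustering, where both the number of counsellors and the ICC are assumed. In a separate simulation of the full GEE, four counsellors with ICC 0.02 to 0.05 gave 9.3% to 15.5%, but that simulation already rejected 5.9% with no clustering, so its figures cannot be read against 5%.

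**Conclusion.** The point holds in conditional form. Delivery is grouped in one arm, and the stated primary analysis and power table ignore it. If outcomes vary between delivery groups, the participant-level standard error is too small. For workshops, the only grouping whose size the document gives, the likely effect is modest: with k = 5 and an assumed ICC of 0.01 to 0.10, the true standard error is 1% to 10% larger and type I error 5.2% to 7.4%. Counsellor caseload could matter more (6.6% to 13% with 4 counsellors and ICC 0.01 to 0.05), but this rests on two assumed quantities, and the sharing of counsellors is itself inferred. Severity lies between something to consider and something that should be changed.

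**What to change.** 1. **Primary GEE:** use the workshop cohort as the independent cluster for the sandwich variance, and keep controls and intervention participants who attended no workshop as single-person clusters. Each person's repeated measures stay inside the cluster. With workshops of 5 there would be roughly 114/5 ≈ 23 workshop clusters plus the single-person ones, so a small-sample correction is sensible.
2. **Counsellors:** workshop clustering does not cover them, and a counsellor-level sandwich would be unreliable if there are few. Prespecify a sensitivity analysis with a partially nested logistic model: a counsellor random intercept in the intervention arm only, with small-sample degrees of freedom. State in advance that it will be imprecise with few counsellors.
3. **Reporting:** give the number of workshops and counsellors, and the ICCs. If these are near zero, the conclusions barely change and the report shows it.

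**Cost:** a few sentences in the analysis plan, and workshop and counsellor identifiers, which delivery records should hold. The Participant Timeline section says analyses were only starting at submission, so the choice should be fixed before results by arm are seen. The price is a slightly wider confidence interval and some loss of power.

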**Session one**	
• Welcome and introduction • Assessment • Vision of the future • Introduction to goal setting • Setting health-related goals	• Overview of intervention • Discuss personal history and health care history • Assess understanding HIV treatment and adherence • Discuss substance use and impact on health and HIV • Identify vision of future healthy self • Goal setting basics • Recalling and amplifying a gender affirming experience
**Session two**	
• Strengths and resiliency • Workshop preparation	• Review goal • Discuss role personal strengths • Set attainable goals • Reviews vision of the future • Discuss expectations of workshop • Create a list of questions for providers at workshop • Recalling and amplifying a gender affirming experience
**Session three**	
• Workshop review • Communication • Communication and health	• Review goal • Feedback on experience of workshop • Discuss remaining questions and areas to clarify • Discuss communication with health care providers • Discuss impact of transphobia, stigma-related trauma • Learn about fight or flight response • Strategize to decrease distress re: provider visits • Rehearse communicating with provider • Recalling and amplifying a gender affirming experience
**Session four**	
• Support and health • Relationships/keeping you and the ones you love safe	• Review goal • Identify current sources of support • Discuss beliefs around autonomy • Identify impact of transphobia, stigma-related trauma • Identify current self-care strategies • Discuss substance use impact on self-care • Identify resources for support • Set goals to increase self-care and access • Recalling and amplifying a gender affirming experience
**Session five**	
• Recognizing and celebrating progress • Recognizing and addressing barriers to improving health	• Review goal • Identify successes and challenges • Problem-solves barriers to completing goals • Identify additional resources • Recalling and amplifying a gender affirming experience
**Sessions six**	
• Review of intervention • Planning for future health	• Review goal • Identify progress • Review skills learned in intervention • Revisit vision of future healthy self • Participant sets goals for future • Participant visualizes achieving goals
**Group workshop (to occur within 3 months)**	
• Gender care & HIV care • Treatment adherence • Provider relations	• Providers discuss gender health, hormone therapy, other gender related treatments and accessing care • Providers discuss HIV, medications and adherence • Q and A between participants and providers • Discuss maximizing relationships with health providers • Relaxation/ breath awareness exercise

Individual sessions with the peer counsellor used consistent opening content, discussion points, and methods for generating individualized content from the participant's unique circumstances. Individual sessions also employed skills training which, depending on the session's focus, include role-playing, behavior rehearsal or practice exercises, and communication problem-solving. The group workshop provided an opportunity for participants to share experiences, brainstorm solutions with each other and with a provider to barriers to accessing health care and to optimal adherence and ask questions and receive accurate information. Workshop topics were generated by the participants and tailored to address their concerns, and included information about hormones and HIV treatment, transphobia, experiences with healthcare, concerns about HIV treatment, and how to communicate effectively with providers. In summary, the *Healthy Divas* intervention includes specific issues relevant to TWH and is organized along the constructs of the models of GA and HCE (see Table 2 for Outcomes and measures).

**Table 2 T2:** Outcomes and measures.

	**Domain**	**Measure (reference)**	**# items**	**α**
**Primary outcome**	Virologic control	COBAS® AmpliPrep/COBAS® TaqMan® HIV test kit (Roche Molecular Systems, Inc.); threshold for undetectability = < 20 copies/mL.	NA	NA
**Secondary outcomes and intervention mechanisms (mediators)**	Treatment engagement	Behavioral composite of engagement in HIV care:1. Current/Past ART use2. HIV appointments timeline follow back3. ART adherence (Lu et al. rating (48) and Walsh VAS) (49)4. Knowledge of current CD4 cell count	10	0.74–0.85
	Gender affirmation	Previously created in K08 research (e.g., current hormone use, access to trans-related health care)	22	0.74
	Health care empowerment	Two subscales (ICCE and TU) (40)	8	0.85–0.90
	HIV treatment knowledge/beliefs	Balfour HIV treatment knowledge (50)Beliefs about medications wuestionnaire (BMQ) (51)Consequences of non-adherence (52)	8 12 4	0.82–0.90
	Adherence self-efficacy	HIV-ASES (53)	12	0.74–0.90
	Treatment readiness	ART expectancies/readiness (54)	12	0.81–0.88
	Social support	Social support questionnaire (55)	6	0.94
	Coping	Coping self-efficacy scale (56)	13	0.80
	Patient communication	Patient communication index (57)	5	0.85
	Shared decision making	Autonomy preference index (58)Decision-making opportunity scale (59)Decisional balance (single item) (60)	6 3 1	0.82–0.84
**Background and potential moderators**	Background/demographic	Age, race, ethnicity, income, education, sex work, relationship status, housing stability, incarceration history, transgender-specific health care, CD4+ cell.	18	NA
	Experiences of transphobia	Experiences of transphobia (adapted from schedule of racist events) (61)	18	0.96
	Experiences of racism	schedule of racist events (61)	18	0.91
	History of trauma	Trauma history questionnaire (62)Recent trauma screening item (63)	24 1	0.85 NA
	Positive and negative affect	Depressive symptoms: CES-D scale (64)Positive / negative affect: differential Emotions scale (DES) (65, 66)	20 30	0.86–0.91
	HIV stigma	HIV Stigma Scale Sowell (67, 68)	12	0.86
	Substance use	DAST-10 (drug screening) (69)Alcohol use disorders identification test (AUDIT) (70)Drug use frequency (71, 72)	10 10 10	0.80–0.94
	Transgender identification	Adapted from multigroup ethnic identity measure (73)	13	0.82

Intervention delivery training included detailed review of the intervention approach, procedures, and research ethics. Population-specific training included how to address trans-specific issues and cultural issues specific to African American and Latina TWH. Specific techniques for adhering to a manualized intervention while allowing for flexibility to address individual participant needs were be taught, role-played and supplemented by instructional readings including one written by Co-I [name] (74). Ongoing training provided updates on HIV treatment and weekly group supervision; individual supervision addressed cases and procedural issues in intervention implementation. In this RCT, we offered the study in both English and Spanish.

